### Control group

Women in the control group will not receive antimicrobial mouth rinse but will instead receive a package consisting of tooth brush and paste, plus oral hygiene education. In the third trimester, women in the control group will be also asked to have a periodontal re-examination.

### Data collection

#### Baseline data

Prior to the periodontal examination, a questionnaire will be administered to collect information such as demographics, socio-economic status, medical and obstetric history, and oral hygiene, stress, etc.

### Periodontal screening and recording (PSR)

We will use a rapid Periodontal Screening and Recording (PSR) [22] tool for screening and identifying pregnant women with periodontal disease. PSR, developed by the American Academy of Periodontology, was a simple screening method for periodontal disease. In this method, the mouth is divided into sextants, using a ball tipped probe with a color-coded area 3.5 to 5.5 from the tip. The dentist inserts the probe into the periodontal pocket, walks around the circumference of each tooth, and observes the position of the color-coded band in relation to the gingival margin. Only the highest code obtained is recorded, representative for the code of the sextant it belongs to. Measurements are recorded in a special box chart [22–24]. The definition of different code is shown as in Table 1. Participant with at least one code of any sextant equal or above three will be diagnosed with periodontal disease [22]. Problems such as furcation involvement, mobility, muco-gingival issues, and recession should also be recorded.

**Table 1 Tab1:** Definition of the code for each sextant in the mouth [22]

Code	Definition
0	The colored area of the probe is completely visible, representing healthy gingival tissues without bleeding on probing
1	The colored area of the probe is completely visible, without calculus or detective margins, but with bleeding on probing
2	The colored area of the probe is completely visible, with supragingival or subgingival calculus and/or detective margins.
3	The colored area of the probe is partly visible.
4	The colored area of the probe is completely invisible, indicating a probing depth greater than 5.5 mm.

All periodontal measurements will be performed by one dentist who will be blinded to the group allocation of pregnant women to ensure study reliability. A dental nurse will record the codes of periodontal screening and other conditions detected during the dental examination.

Prior to the enrollment, the dentist will be invited to participate in a calibration study. Five volunteers will be recruited and will be examined by both the research dentist and an experienced periodontist. Inter- and intra-examiner variations in codes of periodontal screening will be identified between the dentist and the experienced periodontist. They will discuss the difference and adjust the measurement approach until a final agreement is reached.

### Records of use of mouth rinse

All pregnant women in the intervention group will be provided with dairy form to record their daily usage of mouth rinse. At the time of dispensing the mouth rinse each month, the research nurse will collect the diary of the last month from pregnant women. We will calculate the percentage of women who have completed the scheduled use of mouth rinse (twice a day) to assess women’s acceptability and compliance of the use of the supplied mouthwash.

### Follow-up of birth and neonatal outcomes

We will follow up with the recruited women until their childbirth to evaluate their acceptability and compliance to the use of the mouth rinse and to assess their periodontal health status again before the childbirth. Medical records of pregnant women will be reviewed by the research nurse to extract information on birth outcomes including birth weight and gestational age. Prior pregnancy and reproductive history and adverse events during pregnancy will be documented. At the child health care clinic of 42 postnatal days, a questionnaire survey will be carried out by the research nurse to obtain newborns’ health information from birthday to 42 days postpartum.

### Sample size

#### Sample size calculation for primary outcomes

We calculated that a consecutive sample of 422 (211 in each arm of the study) pregnant women with periodontal disease will be required for the study, at 0.05 significance level with 80 % power. The sample size calculation is based on detecting changes in primary outcome of birthweight. To detect a difference in mean birthweight of 100 g between the groups, a sample size of 211 for each group is needed. This was based on an estimation of SD as 380 g in the intervention group and SD as 350 g in the control group. Given the estimated 10 % of loss to following up during pregnancy, a total of 468 women in early pregnancy with periodontal disease will be needed. With the estimation of 75 % prevalence of periodontal disease (from another study in urban area) [17], 624 women in early pregnancy will be recruited for periodontal disease screening. A total of 234 pregnant women with periodontal disease will be needed, at 0.05 significance level with 80 % power, if the sample size calculation is based on changes in mean gestational week to detect a difference of 0.5 week between two groups, with SD 1.5 week and 1.2 week in each group respectively. We use the larger sample size as the final amount for recruiting.

#### Calculation of statistical power for secondary outcomes

The power calculations for secondary outcomes include mean periodontal disease measurements—total periodontal code and rate of admission to NICU.

### Periodontal code

Given the initial sample size of 211 in each group for detecting differences in periodontal code between the intervention and control groups, the proposed study will have 99.9 % statistical power to detect a difference in periodontal code of 3, with a SD as 6 and 5 in each group respectively, at 0.05 significance level.

### Rate of admission to NICU

Given the sample size of 211 in each group, the proposed study will have 60.1 % statistical power to detect an Odds Ratio of 0.5 between two groups, with estimated rate of admission to NICU 15 % for the control group, at 0.05 significance level.

### Data management

Considering the nature of the intervention, participants will not be blinded to their group allocation. The dentist who is going to perform the baseline and final periodontal examination will be blinded for the group allocation.

All materials containing individual information of participants will be stored in a locked cabinet and only research team members will have the access. The computer with research information and data will be password protected and only authorized research team members will be able to access.

### Data analysis plan

Descriptive statistics will be performed to examine for all outcomes and covariates. For continuous variables, such as periodontal code, birth weight (gram), gestational age (week) will be compared using t-tests, or non-parametric equivalents for non-normally distributed variables. For categorical variables such as the rate of periodontal disease and rate of admission to NICU, chi-squared tests will be used. All outcomes will be compared between the intervention and control groups. All analyses will be conducted with “intention to treat” analysis [25].

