### We hypothesize that the MRI will

increase birth weight and prolong gestational duration;reduce progression of periodontal disease during pregnancy;improve neonatal health; andbe acceptable and applicable in resource limited rural areas.

The primary outcomes are mean birth weight (grams) and mean gestational age (weeks). The secondary outcomes are periodontal index determined by the total code of periodontal examination in each sextant of the mouth, compliance of the use of antimicrobial mouth rinse, and rate of admission to Neonatal Intensive Unit (NICU).

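### Continuous outcomes are compared without baseline adjustment although the baseline periodontal code and obstetric history are collected: a loss of precision, not a bias

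*Protocol article*

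**What the plan says.** The protocol article's Data analysis plan names the tests: "For continuous variables, such as periodontal code, birth weight (gram), gestational age (week) will be compared using t-tests", "or non-parametric equivalents for non-normally distributed variables". Covariates appear there only in a descriptive role: "Descriptive statistics will be performed to examine for all outcomes and covariates". No regression model, ANCOVA or change score is named anywhere in the article. The sample size and power sections are likewise unadjusted two-sample calculations.

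The material for adjustment is already part of the design:

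- The periodontal examination determines eligibility for randomisation (Participants and recruitment; Periodontal screening and recording), so a baseline code exists for every randomised woman. The late-pregnancy score comes from the same examiner: "The dentist who is going to perform the baseline and final periodontal examination will be blinded for the group allocation".
- Before that examination, "a questionnaire will be administered to collect information such as demographics, socio-economic status, medical and obstetric history" (Baseline data). The follow-up section adds prior pregnancy and reproductive history.

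One hypothesis is that the rinse will "reduce progression of periodontal disease during pregnancy". The matching secondary outcome is a "periodontal index determined by the total code of periodontal examination in each sextant of the mouth", which is a total and is not defined as a change.

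**The concern.** A pre-randomisation measurement of the same quantity is usually the best single predictor of the follow-up value, and the plan gives it no role. The same holds, more weakly, for maternal and obstetric history as predictors of birth weight and gestational age. Using such variables removes explained variation from the residual and narrows the confidence interval with the same women.

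This matters most for birth weight. It sets the sample size, is powered at only 80 %, and the Discussion concedes that funding limits the size of the trial. For the periodontal code there is also an ambiguity: the Data analysis plan does not say whether the value tested is the late-pregnancy code or its change from baseline. ANCOVA settles that and, in large samples, is at least as precise as either choice.

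**Working it through.** **Inputs from the protocol.** Birth weight: difference 100 g, SDs 380 and 350 g, 211 per arm, "at 0.05 significance level with 80 % power". Gestational age: difference 0.5 week, SDs 1.5 and 1.2. Periodontal code: difference 3, SDs 6 and 5, 211 per arm, stated power 99.9 %. Sidedness is not stated; two-sided 0.05 reproduces the figures.

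**Assumed, because the protocol gives neither.** r, the correlation of baseline with late-pregnancy code: 0.3 to 0.7. R², the share of birth-weight or gestational-age variance explained by covariates: 5 to 20 %.

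**1. Reproduce the plan's own figures (unadjusted).** Root-mean-square SD = √((s₁² + s₂²)/2); n per arm = 2(1.96 + 0.842)² SD²/Δ².

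- Birth weight: SD = √((380² + 350²)/2) = 365.3 g. This gives n = 210 by the normal approximation and 211 by the t distribution (stated: 211). Power at 211 per arm: SE = 365.3 × √(2/211) = 35.6 g, and Φ(100/35.6 − 1.96) = 80.3 %.
- Gestational age: SD = 1.358 weeks, giving 232 in total by the normal approximation and 234 by the t distribution (stated: 234). Power at 211 per arm is 96.6 %.
- Periodontal code: SD = √((36 + 25)/2) = 5.52, SE = 0.538, power for 3 points 99.99 % (stated: 99.9 %).

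The sample size is therefore consistent with the unadjusted tests.

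**2. Birth weight and gestational age with covariates.** The residual SD is multiplied by √(1 − R²).

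| R² (assumed) | Birth-weight power at 211/arm | Difference detectable at 80 % power | Gestational-age power |
|---|---|---|---|
| 0 | 80.3 % | 99.6 g | 96.6 % |
| 5 % | 82.2 % | 97.1 g | 97.3 % |
| 10 % | 84.2 % | 94.5 g | 97.9 % |
| 20 % | 88.2 % | 89.1 g | 98.8 % |

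At R² = 10 %, the equivalent sample is 1/0.9 = 1.11 times as large.

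**3. Periodontal code by ANCOVA.** The variance is multiplied by 1 − r² and the SE by √(1 − r²). For a change score the variance factor is 2(1 − r), if the SD is the same at both examinations.

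| r (assumed) | SE ratio, ANCOVA | Variance factor, ANCOVA / change score | Difference detectable at 80 % power | Power for 1.5 points |
|---|---|---|---|---|
| unadjusted | 1 | – | 1.51 | 79.7 % |
| 0.3 | 0.954 | 0.91 / 1.40 | 1.44 | 83.3 % |
| 0.5 | 0.866 | 0.75 / 1.00 | 1.30 | 89.6 % |
| 0.7 | 0.714 | 0.51 / 0.60 | 1.08 | 97.4 % |

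At the planned 3 points, power exceeds 99.9 % with or without adjustment. The change score is less precise than the plain follow-up comparison when r is below 0.5, and less precise than ANCOVA at every r shown.

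**4. Is the target the same?** Let Y₀ be the baseline code and Y₁ the late-pregnancy code. Randomisation makes the expected Y₀ equal in both arms. The expected between-arm difference in Y₁ therefore equals that in Y₁ − Y₀. The t-test, the change score and ANCOVA all estimate this one quantity, with different precision.

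**The case against.** The strongest reply is that nothing in the plan is invalid. The trial is randomised, the tests match the sample-size calculation, and a condensed article need not list a covariate set. Gestational age and the code are already well powered at the planned differences, the birth-weight gain is modest, and every gain rests on assumed values. The eligibility rule, which requires a code of three or more in at least one sextant, restricts the baseline range and would tend to lower r. Much of this stands. The missing covariate list is indeed no fault. But the article does more than stay silent: it names unadjusted tests for both primary outcomes.

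Three stronger readings are tempting, and the document supports none of them.

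- *Progression goes untested.* A reader might infer this because the hypothesis speaks of progression and the test omits the baseline. Step 4 shows that the between-arm contrast is the same. Nor does the plan say that the late-pregnancy value rather than the change is what will be tested.
- *Chance imbalance biases the result.* The article mentions no stratification. If the baseline SD is about 5.5, chance alone could separate the arms by ±1.05 code points (1.96 × 0.538), and at r of 0.3 to 0.7 some 0.32 to 0.74 points would carry over to follow-up. The standard error and error rate of the unadjusted test already allow for this, so it is noise that adjustment can remove and not bias.
- *Specific predictors are known to be on file.* Parity and previous preterm or low-birth-weight birth are plausible parts of an obstetric history, but the article does not name them.

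It would also be inexact to say that only t-tests are planned. The non-parametric fallback is part of the plan, though it is unadjusted too.

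**Conclusion.** The point holds as an improvement in efficiency. The plan names valid but unadjusted tests while the trial collects, by design, baseline information that would sharpen them. For birth weight the gain is about 2 to 8 percentage points of power (80.3 % to between 82.2 % and 88.2 %) if covariates explain 5 to 20 % of the variance; if they explain almost nothing, almost nothing is gained. For the code, the SE falls by 5, 13 or 29 % at r of 0.3, 0.5 or 0.7. At the planned 3-point difference that means a narrower interval with no useful gain in power; it affects power only for differences of about 1 to 1.5 points. For gestational age the gain is about 1 to 2 points, on power already near 97 %. There is no bias, no error in the sample size and no failure to address the progression hypothesis.

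**What to change.** Before any comparison by arm is seen, state in the analysis plan:

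1. **Periodontal code:** ANCOVA of the late-pregnancy total code on arm and baseline total code.
2. **Birth weight and gestational age:** linear regression on arm plus a short, named set of baseline covariates already collected. Examples are maternal age, baseline total code, and one or two obstetric-history items that the sponsor confirms are recorded. Items about earlier births are undefined for women in a first pregnancy, who need their own category.
3. **Reporting:** the adjusted mean difference with a robust 95 % confidence interval, since the planned SDs differ between arms and the outcomes may not be normal.
4. **Supporting analysis:** the unadjusted t-test or rank-based comparison now planned.

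The cost is wording in the analysis plan, plus a check of the questionnaire for the items to be named. It needs no new data, visits or women. The stated 211 per arm can remain as a conservative figure.

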### Data safety monitoring plan

A Data Safety Monitoring Plan and an independent Data Safety and Monitoring Board (DSMB) have been developed and established to ensure the safety of research participants and the validity and integrity of data. The major responsibilities of the DSMB are to develop protocol stopping guidelines related to the safety of individuals and the overall trial.

## Discussion

We proposed to conduct a RCT to assess a MRI among pregnant women to prevent the progression of periodontal disease during pregnancy and to improve birth and neonatal outcomes. As perinatal oral health care usually not available in rural China, our proposed intervention will be the first study aiming to explore a convenient, affordable, acceptable oral health care package in rural China. If the intervention is effective, it will be more acceptable than the conventional and standard periodontal therapy by women, and have potential generalizability to other similar poor areas, where childbearing aged or pregnant women have very limited access to oral health care.

The conventional periodontal therapy mainly includes “SRP,” which involves mechanically cleaning the teeth above and below the gum line by removing the etiologic agents that cause inflammation. However, due to the high cost, the demand for expensive dental equipment, and the need for professional dentists in order to perform periodontal therapy, as well as concerns regarding the safety of the therapy, this conventional periodontal therapy may not be feasible to apply in low resource settings. In addition, we use a rapid PSR for the screening periodontal disease. Compared to the conventional full-mouth dental examination, the PSR takes only a few minutes to conduct for each patient, does not require the use of expensive dental equipment, and can be performed by non-oral health professionals after receiving appropriate training, which is particularly applicable to economically poor regions. The proposed non-alcohol, 0.07 % CPC antimicrobial mouth rinse is commercially available and cheap; and it has been previously shown to be safe and to decrease the severity of periodontal disease and the rate of preterm birth and low birth weight [21].

Due to limited the research funding and study period, the sample size of this study is relatively small, not allowing for the observation of the birth outcomes as proportions e.g. the rate of low birth weight and the rate of preterm birth. If there is evidence of effectiveness after this initial study, we will seek further funding to expand the trial, with birth outcomes in proportions as primary outcomes.

In summary, our proposed MRI could be a simple, cost-effective, and sustainable solution to improve both mother’s oral health and neonate outcomes. If the mouth rinse is confirmed to be effective, it would demonstrate great potential for the application in other low- or middle-income countries to prevent adverse pregnancy outcomes such as preterm birth and low birth weight and to reduce neonatal and infant mortality.

## Abbreviations

CPC: cetylpyridinium chloride
DSMB: data safety and monitoring board
MRI: mouth rinse intervention
NICU: neonatal intensive unit
PSR: periodontal screening and recording
RCT: randomized controlled trial
SRP: scaling and root planning
